### Sample size

There are currently 6518 students enrolled in the 10^th^ and 11^th^ grades in State-financed schools in the commune of Santiago. Using a 99% confidence level and a 5% error margin, the sample framework is 605 students, which will be divided into the study and control groups. The statistical power is determined using an analysis of variance with a significance level of 0.05, a sample size of 605 and an expected difference of 0.2 points between groups, which will provide a statistical power of at least 0.8. The 0.2 difference is the smallest reported in previous studies comparing the scores of two groups with the instruments that will be used; it was reported in the analysis of the scores of the scale of ambivalent sexism [24].

The statistical power was calculated using the software G*Power [25]. After making a slight adjustment due to the number of students currently enrolled in each school at each level, the definitive size of the experimental phase of the study will be 609 students.

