### Outcomes

Before implementing the workshop, we will perform a base-level measurement of the variables in the students. Later we will measure the result variables in two moments, just after the workshop closes and 3 months after the closure, in order to evaluate the results obtained by the intervention, to determine the effect of the program.

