### Analytical methods

The information that results from the application of the scales will be summarized with descriptive statistics (frequency table, mean, standard error, and asymmetry coefficient) for the pre- and post-intervention evaluations.

Since the intervention has specific objectives for each session, it is not appropriate to impute missing data. However, to account for the potential lack of adherence by some students, it is suggested that participants who miss more than 30% of the sessions should not be included in the data analysis. Regardless of attendance, students will be able to participate in all workshop activities.

We will compare the three evaluations, incorporating information relative to the type of school and course. If the data are normally distributed, we will perform one-way ANOVAs, incorporating post hoc information of the results when necessary, and perform pair-wise comparisons using the Tukey or Games-Howell test.

After the variables with main effects are established, we will perform a factorial ANOVA, in which one of the factors will be fixed (i.e., type of school) and the other will be the repeated measures of the three evaluations. As well as evaluating if the main effects are sustained over time, this will evaluate possible interactions among the studied factors. In this case, following the guidelines proposed by Cohen^75^ for ANOVAs with two or more factors, the effect size will be reported as the partial Eta^2^ statistic. The interpretation of the effect sizes will consider the suggestions of Cohen [50]. These analyses will use the program Jamovi version 1.2 [51].

No interim data analysis will be conducted, and there will be no stopping guidelines.

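### The planned ANOVAs do not secure an arm comparison that uses the baseline score: baseline enters only as one level of a repeated factor crossed with type of school, and study arm is not named

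*Protocol article*

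**What the plan says.** Under Outcomes the protocol commits to a baseline: "Before implementing the workshop, we will perform a base-level measurement of the variables in the students". Two further measurements follow, at the close of the workshop and 3 months later, and each result variable is worded as a change in a construct.

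Analytical methods sets out two steps.

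- One-way ANOVAs, with Tukey or Games-Howell pair-wise comparisons. The section says it will compare the three evaluations and bring in type of school and course. It does not say what the levels of the one-way factor are, and it names no covariate.
- A factorial ANOVA, run once variables with main effects have been identified, in which "one of the factors will be fixed (i.e., type of school) and the other will be the repeated measures of the three evaluations". Interactions among the factors are to be examined, and "the effect size will be reported as the partial Eta" squared statistic.

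Study arm is named in neither step, and neither has a term for school as the allocated unit. Participants: eligibility criteria says schools are randomly assigned to study and control, and Table 1 shows ten schools, five per arm.

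**The concern.** With five schools per arm, the two arms will differ at baseline by chance, on top of chance differences between students. The baseline score is the natural tool against this, and it is already being collected.

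As written, the analysis does not fix how that score serves the arm comparison:

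- If the factorial model is read literally, the interaction tested is type of school by time, which is not the trial's question.
- If arm is supplied as a factor, its main effect is averaged over three evaluations, one of them pre-intervention. That brings in any baseline imbalance and dilutes a real effect.
- The arm-by-time interaction would be the useful term. With three time levels it is an omnibus test, and it is reached only for variables that showed main effects in the earlier, covariate-free ANOVAs.
- Partial eta squared says neither which arm did better nor by how much at post or at 3 months.

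At stake are precision, protection against chance imbalance and an interpretable estimate, in a trial where ten schools already limit all three.

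**Working it through.** **The plan's own figures.** "Using a 99% confidence level and a 5% error margin, the sample framework is 605 students", from 6518 enrolled. With p = 0.5 and z = 2.58, n0 = 2.58² × 0.25 / 0.05² = 665.64, and 665.64 / (1 + 664.64/6518) = 604.05, rounded up to 605. So N is reproduced. The power statement is for an ANOVA tested at the 5% level; it assumes "a sample size of 605 and an expected difference of 0.2 points between groups" and claims that 80% power or more is reached. No SD is given. Read as d = 0.2, two-sided, with no clustering, power is 0.69; one-sided it is 0.79; read as Cohen's f = 0.2 it is 0.998. The calculation as described mentions no baseline covariate.

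**Inputs for the comparison.** From the protocol: five schools per arm and 609/10 ≈ 61 students per school. Assumed, because the protocol gives none: the ICC, the student-level baseline-to-follow-up correlation (ri) and the school-level one (rc). Scores are in SD units.

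**Formulas.** SE of the arm difference = √(2v/5), where v is the variance of one school's mean:

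- post score only: v = ICC + (1−ICC)/61
- change from baseline: v = 2[ICC(1−rc) + (1−ICC)(1−ri)/61]
- student's own baseline as covariate, slope about ri: v = ICC(1 − 2·ri·rc + ri²) + (1−ICC)(1−ri²)/61

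**Worked case, ICC 0.05, ri 0.6, rc 0.8.**

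- Post: v = 0.05 + 0.95/61 = 0.0656, SE 0.162.
- Change: v = 2[0.05 × 0.2 + 0.95 × 0.4/61] = 0.0325, SE 0.114.
- Adjusted: v = 0.05(1 − 0.96 + 0.36) + 0.95 × 0.64/61 = 0.0200 + 0.0100 = 0.0300, SE 0.109.

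| ICC, ri, rc | Post only | Change | Adjusted | Adjusted v post | Adjusted v change |
|---|---|---|---|---|---|
| 0.05, 0.6, 0.8 | 0.162 | 0.114 | 0.109 | −32% | −4% |
| 0.02, 0.5, 0.7 | 0.120 | 0.106 | 0.096 | −20% | −9% |
| 0.05, 0.5, 0.5 | 0.162 | 0.162 | 0.140 | −13% | −13% |
| 0.05, 0.6, 0.9 | 0.162 | 0.095 | 0.098 | −40% | +3% |

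A simulation of school means agreed with all four rows to within 0.001.

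**If the school-mean baseline is also fitted.** Its slope then has to be estimated from ten schools. With v0 = ICC + (1−ICC)/61 and c = ICC·rc + (1−ICC)·ri/61, the variance becomes (v0 − c²/v0) × 7/6. The factor 7/6 is the cost of estimating the slope: 1 + 1/(8−2), with 8 between-school degrees of freedom. For the first three rows the SEs are 0.115, 0.103 and 0.152. Against change, that is 1% worse, 3% better and 6% better, before going from 8 to 7 degrees of freedom.

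**False positives.** Simulated on the Table 1 school sizes with ri = 0.5 and rc from 0.5 to 0.95 (nominal 5%):

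| Analysis | ICC 0.02 | ICC 0.10 |
|---|---|---|
| Students, post score only | 18-19% | 46-47% |
| Students, baseline as covariate | 11-18% | 29-46% |
| School means, with or without baseline | about 4-6% | about 5-6% |

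At ICC 0.05 and d = 0.2, power of the school-level analysis is 0.19-0.21 unadjusted and 0.21-0.47 with baseline adjustment; the gain grows with the school-level correlation.

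**The case against.** The strongest reply is that baseline is not ignored. It is one of the three repeated evaluations, interactions are to be examined, and the outcomes are worded as changes. An arm-by-time contrast removes a constant baseline difference. This stands: a reader might infer that the plan never uses baseline, and the text does not support that. What the reply cannot supply is the arm term, because the factor named is type of school.

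A reader might also infer that the arms will be compared on raw post scores. The text does not clearly say so; the one-way factor could be evaluation, school type or course. The gain against change is therefore the fairer yardstick, and it is the smaller one.

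Nor is adjustment always more precise than change. At a school-level correlation of about 0.9, or with a school-mean slope estimated from ten schools, the advantage can vanish or reverse slightly.

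Finally, it is tempting to blame the missing covariate for chance school differences passing as an effect. The simulation does not support that: student-level adjustment alone still leaves 11-46% false positives over ICC 0.02-0.10. That harm comes from omitting the school term.

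Covariate choice and intervals can be left to an analysis plan that is not shown. But this section already fixes the tests, the factors, the effect-size statistic and the software, so what it fixes is open to comment.

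**Conclusion.** The point holds in a limited form. The plan collects baseline on every outcome but commits neither to an arm-by-time contrast nor to a baseline-adjusted arm comparison, and the effect measure it names carries no direction. Adjusting for the student's own baseline would cut the standard error by about 13-32% against an unadjusted post score and about 4-13% against change, for ICC 0.02-0.05, student-level correlation 0.5-0.6 and school-level correlation 0.5-0.8. All three are assumptions; at a school-level correlation of 0.9, change is about 3% more precise. Valid inference is possible without the covariate, provided school is accounted for. The covariate is a nearly free improvement in precision and in protection against chance imbalance, and it does not replace the school term.

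**What to change.** For each outcome, name one main analysis: a mixed model of the post and 3-month scores with study arm, time and arm by time, and the student's own baseline score as covariate. Add a school random effect, with small-sample degrees of freedom suited to ten schools. Report the arm difference at post and at 3 months, each with a 95% confidence interval, and partial eta squared beside it if wanted. Do not make this analysis conditional on a prior main effect in the one-way ANOVAs.

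The cost is one or two sentences in Analytical methods and a mixed-model routine in place of ANOVA. No new data are needed. Adding the school-mean baseline would cost one between-school degree of freedom and, on the figures above, is not clearly worth it. The wider intervals that come with the school term reflect the design and are not a cost of the baseline covariate.

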### Objectives of the study

The main objective of this study is to evaluate the effectiveness of a preventive-comprehensive program of sexual education in schools directed to students, using a mixed experimental design [23].

Given that comprehensive programs of sexual health have more effective results in attitudes and knowledge, and that a program that incorporates a gender-transformative perspective contributes to equity in sexual health, we hypothesize that the intervention designed and implemented in the experimental group: (i) will increase their sexuality knowledge level; (ii) will increase their preventive sexual behavior (or intentions); (iii) will favor a gender-positive attitude; and (iv) will decrease internalizing and externalizing problems and attention in mental health. The secondary objective is to examine the implementation intervention process, that is, identify the strengths and obstacles in the real context in which the study intervention is performed, to understand the determinants and strategies of the success of the implementation.

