### Participants: eligibility criteria

The intervention will be directed exclusively to students of the 10^th^ and 11^th^ grades who are enrolled in one of the education establishments that depend on the Municipality of Santiago. The inclusion criteria for these schools will be the following: (i) have students of these grades enrolled; (ii) not being an education center oriented to adults or persons deprived of liberty (e.g., closed or semi-closed compounds of Gendarmería de Chile or the National Service for Minors); (iii) have regularity in teaching and learning (for example, schools that were not partially interrupted in 2022 by student manifestations); and (iv) have informed consent of the director. The inclusion criteria for the students will be (i) having 90% or greater attendance in classes: (ii) providing informed consent of voluntary participation; and (iii) having explicit and informed consent of their parents or guardians.

The selected students will be randomly divided into the study and control groups; the intervention will take place in the same schools that the students attend. The assignment to groups will use simple random sampling, performed in two stages. In the first stage, the available schools will be randomly assigned to the study and control groups, while the second stage will randomly select the groups in each school that will participate. The study groups will receive a 10-session intervention in sexual education, covering topics related to preventive sexual conduct, gender equity, and mental health. The control groups will not receive intervention; they will continue with the sexual orientation that each school provides to its students. Sexual orientation is general and is provided by the Ministry of Education. The goal is to evaluate and diagnose the behaviors and reproductive health needs of adolescents, addressing the values adopted regarding the decision to engage in sexual relationships and/or have multiple sexual partners, as well as perceptions of risk.

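### The only fully specified model has type of school and evaluation as its factors, and no planned test names study arm, although the trial is randomised and powered for a difference between arms

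*Protocol article*

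**What the plan says.** All of the following is from the protocol article.

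- **Objectives of the study.** "The main objective of this study is to evaluate the effectiveness of a preventive-comprehensive program of sexual education in schools". The hypotheses follow: "we hypothesize that the intervention designed and implemented in the experimental group" will change four groups of outcomes.
- **Participants: eligibility criteria.** In the first stage, "the available schools will be randomly assigned to the study and control groups". Table 1 has five schools entirely in the control group (308 students) and five entirely in the study group (301).
- **Sample size.** Power of at least 0.8 is claimed from an analysis of variance with "an expected difference of 0.2 points between groups".
- **Analytical methods, first step.** "We will compare the three evaluations, incorporating information relative to the type of school and course". Then: "If the data are normally distributed, we will perform one-way ANOVAs", with Tukey or Games-Howell pairwise comparisons.
- **Analytical methods, second step.** Once variables with main effects have been found, a factorial ANOVA is run in which "one of the factors will be fixed (i.e., type of school) and the other will be the repeated measures of the three evaluations". Besides showing whether main effects last, "this will evaluate possible interactions among the studied factors".

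Analytical methods mentions neither the study group nor the control group. The only classification of the participating schools in the article is the pair of size blocks under Randomization (largest schools; medium and small schools).

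**The concern.** A randomised trial shows effectiveness by comparing the arms. The model as written compares evaluations and types of school. Its possible findings are that scores changed over time, that types of school differ, or that change over time differs by type of school. Unless type of school means arm, none of these isolates the programme.

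Change in both arms without any programme effect is plausible. All students answer the same instruments three times, over ten weekly sessions plus a 3-month follow-up, so they also grow older by more than five months. A common shift could be read as success, and a common drift in the other direction could hide a real effect.

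This is not detail left to a later analysis plan. The article states the factors, introduces the between-student factor with an i.e., and gives the effect-size measure, the post hoc tests and the software. The model is specified, but without the randomised factor.

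**Working it through.** **1. Which tests name arm?**

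| Planned test | Factors named | Arm named? |
|---|---|---|
| Comparison of evaluations | Three evaluations, type of school, course | No |
| One-way ANOVAs and post hoc tests | None in the sentence; the sentence before points to the evaluations | No |
| Factorial ANOVA | Type of school (fixed), three evaluations (repeated) | No |
| Interactions | Among the factors studied, so type of school by evaluation | No |

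**2. The plan's own figure.** The power statement concerns a two-group difference of 0.2 points with 605 students, or 302.5 per arm. The SD is not given. Two-sided power at 0.05 is Φ(0.2/(SD·√(2/302.5)) − 1.96), with √(2/302.5) = 0.0813.

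- SD 1: Φ(2.46 − 1.96) = 0.69.
- SD 0.87: Φ(2.83 − 1.96) = 0.81.

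So the claimed power can be neither confirmed nor refuted. What matters here is that it is the power of a between-arm test, which Analytical methods does not list.

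**3. What the written model would detect.** Assumptions, none from the document: SD 1, within-student correlation 0.5, 304 students per arm, no clustering, type of school balanced across arms, and arm left out of the model. The contrast is the mean of the two later evaluations minus baseline.

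- Variance per student: 0.5/2 + 0.5 = 0.75.
- SE of the overall change: √(0.75/608) = 0.0351.
- SE of the arm difference in change: √(0.75 × 2/304) = 0.0702.
- Expected overall change: drift + ½ × programme effect.

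No effect, common drift 0.2: overall change 0.2, and 0.2/0.0351 = 5.7, so rejection is nearly certain. Effect 0.2, common drift −0.1: overall change −0.1 + 0.1 = 0, so the evaluation test rejects only at its 5% level, whereas the arm difference gives 0.2/0.0702 = 2.85 and power of about Φ(0.89) = 0.81.

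Simulation with 4,000 trials per row (share significant at 0.05):

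| Programme effect, common drift (SD) | Evaluation, arm ignored | Type of school × evaluation | Arm × evaluation |
|---|---|---|---|
| 0, 0 | 5.0% | 5.0% | 4.4% |
| 0, +0.2 | 99.98% | 5.7% | 5.4% |
| 0.2, 0 | 80.6% | 5.0% | 82.3% |
| 0.2, −0.1 | 4.4% | 5.0% | 81.9% |

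The third row does not rescue the evaluation test. An effect of 0.2 with flat controls and a common shift of 0.1 with no effect give the same overall change, 0.1. A second simulation used the three-level repeated-measures test (2,000 trials, 301 versus 308 students, correlations 0.5 and 0.7). It rejected in 71.8% and 91.0% of trials for the first case, and in 73.2% and 91.0% for the second. The test cannot tell them apart.

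**4. Naming arm is not enough.** The 5% level of arm by evaluation in step 3 holds only without clustering. Ten schools are randomised, with 609/10 = 60.9 students each. With design effect DE = 1 + 59.9 × ICC (ICC of the change score, assumed), a nominal 5% test that ignores school rejects in 2[1 − Φ(1.96/√DE)] of null trials:

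| ICC | DE | Actual error rate |
|---|---|---|
| 0.01 | 1.60 | 12% |
| 0.02 | 2.20 | 19% |
| 0.05 | 4.00 | 33% |

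**The case against.** The strongest reply is that a between-arm comparison is clearly intended and the wording is only loose. Much of that stands.

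- **Type of school may mean study school versus control school.** Arm is assigned by school, each school in Table 1 lies wholly in one arm, and the size groups are called blocks, not types. On that reading, the type-by-evaluation interaction is the arm-by-evaluation test. But nothing in the article defines the term so, and a reader cannot tell which test will be run. The sentence needs correcting on either reading.
- **The one-way ANOVA may be between arms.** Its sentence names no grouping factor, and the post hoc tests named are usual for independent groups. This cannot be excluded. All that can be said is that arm is not named.
- **Analyst blinding suggests that groups will be compared.** Agreed. It does not explain the omission, because a coded arm variable can enter a model without revealing which arm is which.

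A reader might go further and infer that the trial will pool both arms, that the control group will go unused, or that the hypotheses commit it to a before-after test. The article supports none of these. Pooling is stated nowhere and is inferred only from silence. Predicting change in the experimental group is ordinary shorthand in a controlled trial. Nor can the ministry's sexual orientation be called a shared influence, since the article describes it only for the control groups.

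**Conclusion.** The point holds as a misstated analysis. The only fully specified model omits the randomised factor, or hides it behind an undefined term, and no listed test matches the comparison on which the trial was sized. Followed literally, the model can credit an ineffective programme (99.98% with a common 0.2 SD shift) and miss an effective one (4.4% with a 0.2 SD effect and a −0.1 SD drift).

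Those rates rest on the assumed drift, SD and within-student correlation, on independent students, and on arm being left out of the model. They illustrate the problem and do not predict this trial's results. The conflict between Analytical methods and the objective, randomisation and power statements does not depend on them. The documents do not show that the investigators mean to ignore the control group. They show that the text does not say how it will be used. Because the omission concerns the test of the main objective, it should be corrected before analysis.

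**What to change.** In Analytical methods, replace the factorial-ANOVA sentence with a statement that:

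1. study arm, under a neutral code so that the analyst stays blind, is the between-group factor, and evaluation is the repeated factor;
2. the effectiveness test is the study-control contrast at post-intervention and at 3 months (arm by evaluation);
3. school, the randomised unit, is accounted for, for example by a random school effect with small-sample degrees of freedom or by an analysis of school-level summaries (10 − 2 = 8 degrees of freedom for an unadjusted comparison of ten school means);
4. size block and grade enter as adjustment factors, and type of school is either defined or dropped;
5. changes over time that are not compared between arms are descriptive and will not support an effectiveness claim.

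The grouping factor of the one-way ANOVAs should be named, or that step removed. Adding a comparison with control to the hypotheses would help clarity but is not essential.

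The cost is wording and slightly more analysis work, with no extra students or data. Intervals will be wider once school is accounted for, which is the price of a valid error rate with ten randomised schools.

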**Assessments**					
Socio-demographic	Personal and home information (ad hoc survey)		x		
	Social network information		X		
Knowledge about sexuality; preventive behavior in sexuality and behavioral intention; empowering and self-efficacy	Knowledge test [46, 47] Survey ad hoc		x	x	x
Gender attitude	Scale of detection of sexism in adolescents (DSA) [48]	x	x	x	x
	Scale of negative attitudes towards trans persons [40]	x	x	x	x
	Short version of Modern Homophobia Scale [41]	x	x	x	x
Mental health	PSC-17 [42]	x	x	x	x

The enrollment, intervention, and assessments are shown in Table 2.

In each intervention session, we will record the attendance and duration, and using structured observation [49], we will record some elements referring to the implementation of the intervention. Those responsible for executing the intervention will receive bi-monthly supervision to control the evaluation and retention.

No specific retention strategy is planned. Available information for students who drop out will include their socio-demographic data, the number of sessions attended, and the results obtained in the tests administered before dropping out.

Because it will be a mixed experimental design GRTs, at the end of the intervention, we will perform a qualitative Case Study to ascertain the experience of the participants and executors with respect to the program and its implementation. Each school of the study group will be a case. The participants will be students who participated in the program and the executors who implemented the intervention. Each case will include focus groups with the students (at least one per case) and semi-structured interviews with the executors (at least two per case). We will then perform a Qualitative Content Analysis to identify certain emergent topics.

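### The repeated-measures ANOVA, with imputation ruled out, uses only students with all three surveys and discards scores already measured; the 605 behind the power statement has no attrition allowance

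*Protocol article*

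**What the plan says.** Analytical methods starts with one-way ANOVAs and pairwise comparisons. It then moves to a factorial ANOVA with a fixed factor, for which type of school is the example given, while "the other will be the repeated measures of the three evaluations". This second model has two tasks: to show whether main effects last over time, and to examine interactions. On missing data the section says that "it is not appropriate to impute missing data", and the reason it gives is that each session has its own objectives.

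The text after Table 2 says "No specific retention strategy is planned". It also says that, for students who drop out, test results obtained up to that point will be available.

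Sample size rests power on "a sample size of 605 and an expected difference of 0.2 points between groups, which will provide a statistical power of at least 0.8". The step from 605 to 609 is explained by enrolment numbers per school and level. Attrition is not mentioned.

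**The concern.** The two rules work against each other. A classical repeated-measures ANOVA needs a score at every level of the within-student factor. If missing scores may not be filled in, a student with a baseline and a post-intervention score but no 3-month score contributes nothing to the model. The protocol expects such partial records and keeps them, but names no longitudinal analysis that can use them. The reason given for not imputing concerns session content and does not justify dropping scores that were measured.

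Two things are at stake. The first is selection: in this model, the change from baseline to post is estimated only in students who also answered three months later, and this applies in both arms. The second is precision: the number analysed is the number with three completed surveys, not the 605 in the power statement.

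The point is separate from the rule that excludes students who miss more than 30% of sessions. That rule can act only in the study arm, because controls have no sessions. The loss described here would remain if the rule were dropped.

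**Working it through.** **Inputs from the document.** Population 6518; 99% confidence and a 5% margin; N = 605 for power; alpha 0.05; a difference of 0.2 points with no SD; power of at least 0.8; planned total 609 (301 study, 308 control); ten schools.

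**Inputs assumed.** Survey completion rates, within-school correlation and the SD. The document gives none of these.

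**1. The plan's own figures.** The finite-population formula for a proportion, with p = 0.5, is n = n0/(1 + (n0 − 1)/6518), where n0 = z² × 0.25/0.05².
- z = 2.576: n0 = 663.6, n = 602.
- z = 2.58: n0 = 665.6, n = 604.

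So 605 is reproduced closely as a survey sample size. Power for a two-group ANOVA at N = 605, two-sided 0.05, depends on how 0.2 is read:
- standardised difference d = 0.2: 0.69
- Cohen's f = 0.2: 0.998
- raw points: 0.80 only if the SD is at most about 0.88, that is d = 0.2/0.878 = 0.228

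**2. Margin against 605.** 609 − 605 = 4, and 4/609 = 0.66%. A loss of five students takes the analysed number below 605.

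**3. What listwise deletion discards.** Assume baseline is complete and 10% are missing independently at each later survey.
- Scores available at each later evaluation: 609 × 0.9 = 548.
- Students with all three surveys: 609 × 0.9² = 493.
- Students with exactly one later score: 609 × 2 × 0.9 × 0.1 = 110. That score is discarded.
- Students with neither later score: 609 × 0.1² = 6.

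At each later evaluation, 548 − 493 = 55 measured scores are therefore lost to the model.

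**4. Size in power.** Take d = 0.228, so that 605 gives 0.80, in a two-group comparison at a single evaluation.

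| Students | Power |
|---|---|
| 605 | 0.80 |
| 548 (all available at that evaluation) | 0.76 |
| 493 (complete cases) | 0.71 |

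The fall from 0.80 to 0.76 is plain non-response, and no choice of model restores it in full. The fall from 0.76 to 0.71, about 4 to 5 points, is the part due to listwise deletion.

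**5. How far this moves.**
- If the same students miss both later surveys, no follow-up score is discarded (only their baseline), and the extra cost to this comparison is nil.
- If 0.2 is Cohen's f, power is 0.993 on 493 students, so the loss is immaterial.
- If d = 0.2, power is 0.65 on 548 and 0.60 on 493, but it was already 0.69 at 605.
- With clustering by school, effective size = N/(1 + (m − 1) × ICC) with m = N/10. At an assumed ICC of 0.05, going from 609 to 493 moves the effective size from 152 to 144 (5%). At 0.01 it moves from 381 to 332 (13%). Without clustering the cut is 19%.

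**The case against.** The strongest reply is that the article names no primary analysis and puts one-way ANOVAs first. If these are run evaluation by evaluation, they keep every observed score. The fixed factor mentioned for the factorial model is type of school, not study arm. A reader might infer that the repeated-measures ANOVA decides the trial, and that every post-intervention comparison is confined to students who answered at 3 months. The text does not support either reading. The restriction holds within the factorial model. That model is still the only one assigned to sustained effects and interactions, and one-way comparisons do not answer those questions.

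A reader might also infer that power must fall below 0.8. The document does not allow that conclusion: it states at least 0.8 and gives no SD, and on one reading power stays at 0.985 even after a 30% loss (426 students). The figures above are also for a single-evaluation comparison, and a repeated-measures contrast may have more or less power depending on the within-student correlation.

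Nor is the absence of a retention strategy the whole picture. The article describes telephone and WhatsApp contact for follow-up, and supervision of the executors that covers retention. High loss should therefore not be presumed.

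Finally, the article never says that only complete cases will be used, and a separate analysis plan might deal with partial records. But the complete-case restriction follows from the method and the no-imputation rule, both of which the article states. It is a choice already made, not a detail left open.

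**Conclusion.** The point holds as a matter of method. The model assigned to sustained effects and interactions drops any student who lacks one survey. It discards scores that the protocol says are kept, and rests its comparisons over time on completers in both arms. Its analysed number falls below 605 once loss exceeds about 0.7%.

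The cost in power is modest and conditional. It is about 4 to 5 points if 605 gives exactly 0.80 and 10% are missing independently at each later survey. It is less with clustering, nil for the follow-up comparison if the same students miss both later surveys, and negligible if 0.2 is Cohen's f. The loss of observed data and the selection of completers do not depend on the SD, and they are the main reason to change the analysis.

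**What to change.** Replace the repeated-measures ANOVA with a likelihood-based linear mixed model. Use fixed effects for arm, evaluation and arm by evaluation, with random effects for student, course and school, and fit it to every observed score. No imputation is needed, so the plan's position on that is respected, and a missed survey costs only that one score. The model is valid under missingness at random, which is a weaker condition than the complete-case analysis needs. Keep the complete-case ANOVA as a sensitivity analysis if wanted.

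The change affects analysis wording only and needs no new data. The small downside is that partial eta-squared gives way to model-based mean differences with confidence intervals.
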